### Exclusion criteria

2.6

(1) Recent psoriasis treatments, including systemic therapy (e.g., cyclosporine, methotrexate), phototherapy, traditional Chinese medicine, or small-molecule targeted agents within 1 month or biologic agents within 3 months prior to enrollment.(2) Presence of clinically significant comorbidities, such as coagulation disorders, infectious diseases, psychiatric conditions, autoimmune diseases, malignancies, or major organ dysfunction.(3) Significant weight fluctuation or notable body shape alteration within the past 3 months.(4) Active weight-loss interventions (e.g., dietary control, supplements, regular exercise) accompanied by weight reduction within the past 3 months.(5) History of keloid formation or hypertrophic scarring.(6) Participation in any other clinical trial within the past 6 months.(7) Pregnancy, lactation, or planned pregnancy during the study period.(8) Patients with needle phobia.(9) Inability or unwillingness to comply with the intervention, attend scheduled follow-ups, or complete required study procedures.(10) Any other condition considered by the investigators to potentially affect the validity of the study or the safety of the participant.

### Termination criteria

2.7

The entire study will be terminated if:

(1) Serious safety concerns are identified that preclude further participation.(2) The intervention demonstrates negligible efficacy or lacks clinical value.(3) Major protocol deviations occur that compromise data validity.(4) The sponsor terminates the study for administrative or financial reasons.(5) Regulatory authorities mandate study discontinuation.

### Withdrawal criteria

2.8

Participation will be discontinued if any of the following criteria are met:

(1) Failure to attend scheduled outpatient follow-ups on time.(2) Occurrence of serious adverse reactions.(3) Changes in the participant’s medical condition that render continued participation inappropriate.(4) The participant or their legal guardian requests to stop.

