#### Data handling for terminated cases

2.8.1

For participants who are withdrawn, all collected data will be retained in the case report forms. The last available observation will be used as the final outcome for both efficacy and safety analyses.

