**Figure 3 fig3:**
[figure not shown]
ACE needle and absorbed sutures.

For the verum group, the needle will be inserted manually into the selected acupoints. The ST25, SP15, CV12 and ST36 will be punctured perpendicularly, with an insertion depth of approximately 25–35 mm. The BL18 and BL20 will be punctured at a 45°angle to the skin, with an insertion depth of about 15–20 mm. Once the acupoint sensation is achieved, the practitioner withdraws the needle while pushing the absorbable thread into the muscle layer using the needle core. Immediately following, needle withdrawal, the puncture sites will be promptly compressed with sterile dry cotton swabs to prevent bleeding. The placement of the thread depends on the depth of the needling, and the practitioner will not feel any resistance while inserting the absorbable thread. The treatment will be administered once every 2 weeks for a total of four sessions, lasting 8 weeks (24, 34).

For the sham group: using the same disposable needles (with the catgut suture pre-removed), the practitioner performed an identical procedure—insertion into the muscle layer followed by a simulated “pushing-withdrawing” action—ensuring the same tactile experience for participants as the verum group, with the sole difference being the absence of actual suture embedding.

A sham procedure was selected as the control for​ the following reasons: (1) to ensure rigorous trial design: as a double-blind, randomized controlled trial, a sham procedure is essential. It matches the verum ACE in every visible aspect, ensuring effective participant blinding and controlling for non-specific effects (e.g., placebo, natural disease variation). This allows for an objective evaluation of the specific therapeutic effect attributable to the catgut embedding itself. (2) to demonstrate specific efficacy beyond standard care limitations: Current standard treatments for mild psoriasis have limitations, including side effects and lack of efficacy for obesity. This trial aims to prove that ACE offers a specific therapeutic benefit, which necessitates comparison against a non-active intervention to establish its distinct clinical value.

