Participation will be discontinued if any of the following criteria are met: (1) failure to attend scheduled outpatient follow-ups on time; (2) occurrence of serious adverse reactions; (3) changes in the participant’s medical condition that render continued participation inappropriate; (4) the participant or their legal guardian requests to stop.

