### Data collection procedures

2.15

The study comprises an 8 weeks intervention period followed by a 32-week follow-up phase. During the intervention, data collection and clinical assessments will occur biweekly. Post-intervention follow-up evaluations are scheduled every four weeks through week 24, with a final assessment at week 32.

To explore the biological underpinnings of the therapeutic response, peripheral venous blood samples will be collected at baseline (week 0), mid-intervention (week 4), end-of-treatment (week 8), and at the final follow-up (week 32). These supplementary samples will support exploratory multi-omics analyses, including single-cell sequencing, untargeted metabolomics, and proteomics (Figure 4). A comprehensive schedule of all assessment items is provided in Table 1.

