### Retention strategies

2.18

In order to keep the participants involved for as long as possible, we implemented a comprehensive approach which included among others: a logistical support (transportation subsidies, flexible scheduling, and reminders via SMS/phone/WeChat), active engagement (regular health education, a dedicated app for calorie tracking, and personal progress feedback), and a system of rewards (compensation for time and travel at every visit). For those who dropped out, an early termination visit was organized to obtain primary/secondary efficacy outcomes (with consent), safety data, reasons for withdrawal, and final medication records. Data from lost to follow-up participants who had done at least two assessments were considered and counted in the intention-to-treat (ITT) analysis.

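### Sections 2.8 and 2.13 end participation, not only embedding, after a serious adverse reaction, so the scheduled week-8 PASI and BMI of these patients are not measured

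*Protocol article*

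**What the plan says.** Section 2.8 (Withdrawal criteria) opens with "Participation will be discontinued if any of the following criteria are met". Two of its four criteria matter here: "Occurrence of serious adverse reactions", and changes in the "medical condition that render continued participation inappropriate". Section 2.13 lists the same criteria again, including "2) occurrence of serious adverse reactions". Neither section distinguishes stopping the procedure from leaving the study.

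Four other places bear on what happens to the outcome of such a patient:

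- Section 2.8.1 keeps all data collected and adds: "The last available observation will be used as the final outcome for both efficacy and safety analyses".
- Section 2.18 says that for dropouts "an early termination visit was organized to obtain primary/secondary efficacy outcomes (with consent". It gives no time for that visit.
- Section 2.21 promises an analysis by randomised group whatever the adherence, deviations or loss to follow-up. It prefers multiple imputation or mixed-effects models for missing values and names a linear mixed model as the primary analysis, yet ends by prescribing complete cases without imputation.
- Section 2.22, item 5, tells staff to halt the experiment if allergy or shock occurs. It does not say whether that means the procedure or the patient's participation.

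On the difference between the arms, section 2.13 describes the sham as the same needling into muscle, "with the sole difference being the absence of actual suture embedding".

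**The concern.** Both primary endpoints are measured at week 8. An intention-to-treat comparison needs that measurement from patients who stopped treatment as well as from those who finished. The withdrawal rule turns stopping treatment for harm into stopping follow-up, so a patient with a serious reaction before week 8 has no scheduled week-8 PASI or BMI. The analysis must then substitute something for a value that could often have been measured.

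The loss need not be balanced. Needling is common to both arms and the suture is not, so serious reactions specific to the suture can remove patients from the verum arm only. That part of the missingness is related to treatment, and none of the missing-data methods named in the article recovers the true week-8 value.

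There is a safety side too. Documenting adverse events throughout the study is a secondary objective (section 2.4), and Table 2 schedules adverse event checks to week 32. The rule takes out of that schedule the patients whose later course is of most interest. Section 2.14 offers observation and care, but does not restore the scheduled assessments.

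**Working it through.** **1. Is there a route to a week-8 value?** Read together, sections 2.8, 2.8.1, 2.13, 2.14, 2.18, 2.21 and 2.22 give none. The early termination visit yields efficacy outcomes only with consent and is not tied to week 8. Otherwise the value is carried forward (2.8.1), modelled or imputed, or left out (both 2.21).

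**2. The plan's own figures.** Section 2.11 uses 0.60 v 0.25, two-sided alpha 0.05 and 80% power: (1.96 + 0.84)² × (0.60×0.40 + 0.25×0.75) / 0.35² = 7.84 × 0.4275 / 0.1225 = 27.36, rounded up to 28. Then 28 / 0.80 = 35 per group. Both figures reproduce.

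**3. How many patients?** The article gives no rate of serious reactions. For assumed suture-related withdrawal rates among 35 verum patients:

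| Assumed rate | Expected number | Chance of at least one |
|---|---|---|
| 1% | 0.35 | 30% |
| 3% | 1.05 | 66% |
| 5% | 1.75 | 83% |
| 10% | 3.5 | 97% |

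At 1%, no affected patient is the likelier outcome.

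**4. Error from carrying the last value forward.** Let K of 35 verum patients be withdrawn and no sham patients. Let f be the share of the full week-8 change already present in the carried value, and g the share truly present at week 8 after stopping. Taking the full change as 1, the true intention-to-treat verum mean is 1 − (K/35)(1 − g) and the carried-forward mean is 1 − (K/35)(1 − f). The error is (K/35)(f − g).

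Section 2.15 says "During the intervention, data collection and clinical assessments will occur biweekly". On an assumed linear course, f is 0.25, 0.50 or 0.75 for a last value at week 2, 4 or 6. Table 1 lists PASI and BMI during treatment only at weeks 0, 4 and 8, so f = 0 is possible if the early termination visit also yields nothing. Error as a percentage of the full change, shown as K = 1 / K = 3:

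| f | g = 0 | g = 0.5 | g = 1 |
|---|---|---|---|
| 0 | 0 / 0 | −1.4 / −4.3 | −2.9 / −8.6 |
| 0.25 | +0.7 / +2.1 | −0.7 / −2.1 | −2.1 / −6.4 |
| 0.50 | +1.4 / +4.3 | 0 / 0 | −1.4 / −4.3 |
| 0.75 | +2.1 / +6.4 | +0.7 / +2.1 | −0.7 / −2.1 |

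The sign depends on whether the patient would have gone on improving or lost ground. With f and g between 0 and 1, the error cannot exceed K/35: 2.9% for one patient, 8.6% for three.

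**5. Error from leaving the patient out.** On the same scale the complete-case error is (K/35)(1 − g), an overstatement unless g = 1. With g = 0.5 it is 1.4% (K = 1) or 4.3% (K = 3); with g = 0 it is 2.9% or 8.6%. A mixed model or imputation that learns from patients who stayed on treatment errs in the same direction, by no more than about this.

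**6. Power, as a rough guide only.** For the binary comparison of section 2.11, excluding 1 or 3 verum patients moves power from 88.6% (35 v 35) to 88.1% or 87.0%. If the whole dropout allowance of 35 − 28 = 7 per arm is already used, it moves from 80.9% to 80.1% or 78.3%. The primary analysis is a continuous mixed model, so these are not its power.

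**The case against.** The strongest reply is that the event is probably rare and the loss is only partial. Section 2.22 mainly expects local pain, swelling, itching and bowel or appetite changes, and its handling of redness, bruising, expelled sutures and induration does not call for stopping. Data already collected are kept, an early termination visit is planned, and a final value is supplied. All of this stands, and it limits the size.

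It also rules out some stronger readings that a reader might infer:

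- *That the primary outcomes are lost outright.* Sections 2.8.1 and 2.18 do not support this. The week-8 value is replaced by an earlier or modelled one, and disappears only if the complete-case sentence governs.
- *That only the verum arm is affected.* The criterion covers any serious adverse reaction, and sham patients receive the same needling. Only suture-specific reactions are confined to verum.
- *That an allergic reaction ends participation.* Sections 2.8 and 2.13 do not mention allergy, and item 5 of section 2.22 may mean only the procedure.
- *That carrying forward always pulls the effect toward zero.* The error can be zero or of either sign.

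Two further replies carry some weight. The conflict between carrying forward, imputing and complete cases is a separate problem that touches every missing value. And section 2.23 says the complete protocol is a supplement, not shown here, which might arrange follow-up after stopping treatment. The point does not rest on that silence, however: the article states twice, in positive terms, that participation ends.

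**Conclusion.** The point holds in limited form. As worded, the rule creates avoidable missing week-8 values among patients stopped for a serious adverse reaction, part of them related to treatment, and so works against the article's own intention-to-treat aim.

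The size is unknown and probably small. For 1 to 3 affected verum patients, which is an assumption because the number may be zero, the error in the verum mean change is at most 2.9% to 8.6% of the full change. Its direction depends on the method used and on the patient's course after stopping. These figures also assume no sham withdrawals for such reactions and, for intermediate visits, a linear course. Power is not the argument. The case for change is that the missingness is avoidable and cheap to prevent.

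**What to change.** In sections 2.8 and 2.13, state that a serious adverse reaction stops further embedding only and that, unless consent is withdrawn, the patient stays in the study for the scheduled week-8 PASI and BMI assessments and for adverse event follow-up. In section 2.22, item 5, make clear that what is halted is the procedure.

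This is a short wording amendment. It adds no visits or patients, and embedding still stops at once. The cost is some follow-up effort for patients who are off treatment. For every patient who then has a measured week-8 value, the choice among the missing-data methods no longer matters at that visit.

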#### Data handling for terminated cases

2.8.1

For participants who are withdrawn, all collected data will be retained in the case report forms. The last available observation will be used as the final outcome for both efficacy and safety analyses.

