### Statistical methods

2.21

All participants who provided written informed consent and completed baseline assessments will be included in the primary analysis, consistent with the ITT principle. Data will be analyzed according to the group to which participants will be initially randomized, regardless of treatment adherence, protocol deviations, or loss to follow-up, to minimize selection bias and reflect real-world clinical effectiveness. For missing data, a stratified strategy will be adopted: preference will be given to filling in missing values using existing data through multiple imputation or mixed-effects models, while also conducting per-protocol set analyses (including only participants with ≥ 80% compliance) as sensitivity verification; for categorical data, if the proportion of missing values is ≤ 5%, the indicator will be directly excluded, and if it is > 5%, the FIML method will be used.

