All statistical analyses will be performed using a pre-specified statistical analysis plan. The primary analysis will use a linear mixed-effects model for repeated measures to analyze the changes from baseline in the continuous PASI score and BMI at week 8. As these will be pre-specified co-primary endpoints evaluating distinct therapeutic dimensions, no adjustment for multiple will be applied. Each endpoint will be tested independently at a two-sided significance level of *α* = 0.05. A similar approach will be used for continuous secondary outcomes (e.g., DLQI, WC, lipid profiles, inflammatory markers) will be presented as mean ± standard deviation for continuous variables and as frequencies (n) and percentages (%) for categorical variables. Within-group comparisons (e.g., baseline vs. Week 8) will be analyzed using paired t-tests for normally distributed data or Wilcoxon signed-rank tests for non-normally distributed data. Between-group comparisons will be performed using independent samples t-tests or Mann–Whitney U tests. Categorical outcomes will be compared using Chi-square tests (or Fisher’s exact tests). A two-sided *p*-value < 0.05 will be considered statistically significant. All analyses will follow the intention-to-treat principle. For exploratory outcomes assessed at extended time points (Weeks 12, 16, 24, and 32), the analysis will be primarily descriptive. Data are presented as mean ± standard deviation (or median with interquartile range for non-normally distributed data). No formal between-group hypothesis testing will be performed for these time points, as the data will be intended to illustrate long-term trends rather than confirm treatment efficacy. All statistical tests will be two-sided with a significance level of *α* = 0.05.

Pre-specified subgroup analyses will be performed to explore the heterogeneity of treatment effects on the primary outcomes. Interactions between treatment group and the following baseline covariates will be tested using the linear mixed model by including an interaction term: sex (male, female), age (< 45 years, ≥ 45 years), baseline BMI (< 28 kg/m^2^, ≥ 28 kg/m^2^), baseline disease duration (< 5 years, ≥ 5 years)

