Analysis of AEs will be performed on the safety population, summarizing the incidence of adverse events and changes in laboratory parameters by treatment group using descriptive statistics. Formula: AEs rate (%) = (number of participants with a treatment-related adverse reaction / total number of participants receiving the treatment) × 100%. The results of subgroup analyses will be interpreted as exploratory.

No adjustment for multiple comparisons will be made for these analyses.

The analysis will handle missing data using a complete-case approach without imputation.

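### Sections 2.8.1, 2.18 and 2.21 give conflicting missing-data rules and ITT populations, so the week-8 PASI and BMI estimates can depend on which sentence is followed

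*Protocol article*

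**What the plan says.** The protocol article speaks to missing outcomes in three sections.

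- **Section 2.8.1 (Data handling for terminated cases)**, on withdrawn participants: "The last available observation will be used as the final outcome for both efficacy and safety analyses". Section 2.8 counts failure to attend follow-up on time as a reason for withdrawal, so this reaches most people who leave.
- **Section 2.18 (Retention strategies)** plans an early termination visit for those who drop out and adds: "Data from lost to follow-up participants who had done at least two assessments were considered and counted in the intention-to-treat (ITT) analysis".
- **Section 2.21 (Statistical methods), opening paragraph**, on the population: "All participants who provided written informed consent and completed baseline assessments will be included in the primary analysis, consistent with the ITT principle". On missing values: "preference will be given to filling in missing values using existing data through multiple imputation or mixed-effects models". On categorical data: "if the proportion of missing values is ≤ 5%, the indicator will be directly excluded", with FIML above that level.
- **Section 2.21, next paragraph**, naming the model for the week-8 endpoints: "The primary analysis will use a linear mixed-effects model for repeated measures to analyze the changes from baseline in the continuous PASI score and BMI".
- **Section 2.21, last sentence**, after the adverse-event and subgroup statements: "The analysis will handle missing data using a complete-case approach without imputation".

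**The concern.** LOCF, multiple imputation or a mixed model, and complete cases are different estimators. If withdrawn participants' last values are entered as their week-8 outcomes, nothing is left for the mixed model to handle, and a carried value is treated as if it had been measured. If incomplete participants are dropped, the ITT statement is no longer met. An analyst could follow any one of these sentences and claim to have kept to the protocol, and after unblinding that choice could be made with the results in view.

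A statistical analysis plan that is not shown would not remove the problem. The article itself prints incompatible rules, so such a plan would have to contradict at least one published sentence.

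**Working it through.** **1. How many participants the rules touch.** Section 2.11 gives p₁ = 0.60, p₂ = 0.25, 1.96 and 0.84. The printed formula reproduces:

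(1.96 + 0.84)² × (0.60 × 0.40 + 0.25 × 0.75) / 0.35² = 7.84 × 0.4275 / 0.1225 = 27.36, so 28 per group; 28 / 0.80 = 35 per group, 70 in total.

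At 20% dropout, 0.20 × 70 = 14 participants. Section 2.11 does not say when dropout occurs and follow-up runs to week 32, so 14 is the upper figure for week 8 at the planned rate.

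**2. The rules side by side.**

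| Question | One statement | Another statement |
|---|---|---|
| Efficacy outcome of a withdrawn participant | 2.8.1: carry the last value forward | 2.21: multiple imputation or mixed model |
| Missing safety data | 2.8.1: carry the last value forward | 2.21, last sentence: complete cases, if it covers safety |
| Lost participants in ITT | 2.18: those with at least two assessments | 2.21: everyone with baseline data |

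The first row is a direct conflict on the primary analysis. The second conflicts whether the last sentence of 2.21 is read broadly or as limited to adverse events and subgroups. The third concerns who is analysed at all.

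**3. What LOCF does to a BMI difference.** The assumptions, none of them from the documents, are: mean BMI loss at week 8 of 1.5 kg/m² (verum) and 0.5 kg/m² (sham), a true difference of 1.0; a linear course; dropouts share their arm's mean course. Let f be the fraction of the week-8 change reached at the last value, and d_v and d_s the dropout proportions.

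LOCF estimate = 1.5 × [1 − d_v(1 − f)] − 0.5 × [1 − d_s(1 − f)]

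- 20%/20%, just after baseline (f = 0): 1.5 × 0.80 − 0.5 × 0.80 = **0.80**
- 20%/20%, week 4 (f = 0.5): 1.5 × 0.90 − 0.5 × 0.90 = **0.90**
- 20%/20%, week 6 (f = 0.75): 1.5 × 0.95 − 0.5 × 0.95 = **0.95**
- 30%/10%, week 4: 1.5 × 0.85 − 0.5 × 0.95 = **0.80**
- 30%/10%, week 6: 1.5 × 0.925 − 0.5 × 0.975 = **0.90**
- No true effect, both arms losing 1.0, 30%/10%, week 4: 0.85 − 0.95 = **−0.10**

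The week-6 rows need a week-6 value. Section 2.15 says assessments are biweekly during treatment, but Table 1 lists PASI and BMI only at weeks 0, 4 and 8 in that period. On the Table 1 schedule, someone who leaves before week 4 without an early termination visit gets a change of exactly zero under LOCF.

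**4. Whether the rules can diverge from one another.** A simulation with assumed values used 35 per arm, SD 1, a true difference of 0.35 at week 4 and 0.70 at week 8, correlation 0.7, dropout after week 4 more likely with poor early response, and 4,000 runs. Mean estimated week-8 differences were:

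| Dropout, verum/sham | LOCF | Complete case | Estimate using week-4 data (missing at random) |
|---|---|---|---|
| 20%/20% | 0.63 | 0.70 | 0.70 |
| 10%/30% | 0.70 | 0.56 | 0.70 |
| 30%/10% | 0.56 | 0.83 | 0.70 |

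The last column recovers 0.70 because dropout was made to depend on the observed week-4 value. The table shows that the rules can separate, in either direction. It does not forecast this trial.

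**The case against.** The strongest reply is that Section 2.21 already names a mixed model as the primary analysis, so the stray sentences need only tidying. The model is indeed named, and that makes the repair easy. It does not remove the conflict, because Section 2.8.1 expressly applies its rule to efficacy and nothing subordinates it to Section 2.21.

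Several stronger readings are tempting and are not supported:

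- **Complete cases as a certain third rule for the primary result.** The sentence follows the adverse-event and subgroup statements and may cover only those. Its scope is unclear.
- **Unequal withdrawal as likely.** Only verum participants receive sutures, but both arms are needled and the article gives no withdrawal rates by arm. The 30%/10% split is an illustration.
- **80% compliance as four of four sessions.** The article asks for "per-protocol set analyses (including only participants with ≥ 80% compliance) as sensitivity verification" and does not define compliance in sessions. Section 2.12 mentions monitoring compliance alongside a WeChat group, meal photographs and step counts.
- **No sensitivity analysis for the missing-data assumption.** Section 2.21 refers to a pre-specified analysis plan that is not shown, and such analyses may be there.
- **The categorical rule as a threat to the primary result.** Both primary endpoints are analysed as continuous. Read literally, the rule drops a whole indicator when few values are missing, but it may mean that the missing values are excluded. It is a minor wording point.

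The early termination visit in Section 2.18 may reduce the number of missing values. It requires consent and does not say which rule applies to those that remain.

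**Conclusion.** The contradiction stands on the text alone: LOCF in Section 2.8.1 against multiple imputation or a mixed model in Section 2.21, for the same week-8 PASI and BMI analysis. The complete-case sentence adds a conflict of uncertain scope, which even on the narrow reading collides with Section 2.8.1 on safety. Sections 2.18 and 2.21 disagree on who among the lost participants belongs to ITT.

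The primary estimate can therefore depend on the sentence followed; whether it will depends on how many leave, when and why. Up to 14 of 70 participants are affected at the planned rate. Under the assumed linear BMI course, LOCF turns a true 1.0 kg/m² into 0.80 to 0.95 at 20% dropout per arm, and into 0.80 at 30%/10% with week-4 dropout. These sizes rest wholly on assumed effects, timing and dropout splits.

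**What to change.** 1. State one primary rule for week-8 PASI and BMI: the repeated-measures mixed model fitted to all observed visits of all randomised participants, under missing at random.
2. In Section 2.8.1, delete LOCF for efficacy or label it a sensitivity analysis. State separately how safety data of withdrawn participants are summarised, so that deletion leaves no gap.
3. In Section 2.21, delete the complete-case sentence or limit it to named analyses.
4. Align Section 2.18 with Section 2.21 on the ITT population.
5. As a minor wording correction, say in the categorical rule that no indicator is dropped because values are missing.

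The cost is wording only, with no new data and no change in sample size. It should be done before unblinding.

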**Methods:**

This is a multicenter, randomized, double-blind, sham-controlled trial. Participants aged ≥ 18 years with mild plaque psoriasis (PASI< 3, BSA < 3%) and overweight (BMI ≥ 24 kg/m^2^) will be randomized (1:1) to receive either verum ACE at 14 specific acupoints or a sham procedure. Interventions will be administered every 2 weeks for 8 weeks. The primary endpoints are the changes in PASI score and BMI from baseline to week 8. Secondary outcomes include the Dermatology Life Quality Index (DLQI), waist circumference (WC), lipid profiles, and systemic inflammatory markers. The safety of the procedure will be monitored through the recording of adverse events and conducting laboratory tests. Participants will be followed through week 32 to evaluate long-term therapeutic durability.

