### Sample size calculations

2.11

Based on our pilot data, the verum ACE achieved an improvement rate of 60%. Since no sham-controlled acupuncture trials for psoriasis are available, we derived the sham group response rate from the placebo effect observed in psoriasis pharmacological trials, which was approximately 25% as reported in the literature (40). Sample size estimation was performed using the standard formula for comparing two independent proportions (two-sided test, *α* = 0.05, power = 80%):

$$n1=n2=\frac{{\left(Z_{1-\alpha /2}+Z_{1-\beta }\right)}^{2}\times [p_{1}(1-p_{1})+p_{2}(1-p_{2})]}{{\left(p_{1}-p_{2}\right)}^{2}}$$

Where p_1_ = 0.60, p_2_ = 0.25, Z_1 − α/2_ = 1.96, and Z_1 − β_ = 0.84. The calculated sample size was 28 participants per group. After adjusting for a 20% dropout rate, the final sample size was determined to be 35 participants per group (total 70 participants).

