**Figure 4 fig4:**
[figure not shown]
Data node collection diagram.

**Table 1 tab1:** The complete set of assessment items.

Project	0 W	4 W	8 W	12 W	16 W	24 W	32 W
PASI	**×**	**×**	**×**	**×**	**×**	**×**	**×**
BSA	**×**	**×**	**×**	**×**	**×**	**×**	**×**
PGA	**×**	**×**	**×**	**×**	**×**	**×**	**×**
Itch NRS score	**×**	**×**	**×**	**×**	**×**	**×**	**×**
DLQI	**×**	**×**	**×**	**×**	**×**	**×**	**×**
BMI	**×**	**×**	**×**	**×**	**×**	**×**	**×**
WC	**×**	**×**	**×**	**×**	**×**	**×**	**×**
WHR	**×**	**×**	**×**	**×**	**×**	**×**	**×**
Blood pressure	**×**	**×**	**×**	**×**	**×**	**×**	**×**
Traditional Chinese Medicine Syndrome Scoring	**×**	**×**	**×**				
ESR, CRP	**×**	**×**	**×**				**×**
Lipid profile	**×**	**×**	**×**				**×**
Blood glucose	**×**	**×**	**×**				**×**
Blood uric acid	**×**	**×**	**×**				**×**
Peripheral blood sample	**×**	**×**	**×**				**×**

If female, additional baseline blood HCG tests are required.

We will assess the safety of acupoint embedding therapy through the collection of biological sample information, including but not limited to general data, blood pressure, heart rate, and blood sample collection (Table 2).

**Table 2 tab2:** Safety indicators.

Project	0 W	4 W	8 W	12 W	16 W	24 W	32 W
Basic information	**×**						
Medical information	**×**						
Complete blood count	**×**		**×**				
Liver function, kidney function	**×**		**×**				
Electrocardiogram (ECG)	**×**		**×**				
AEs		**×**	**×**	**×**	**×**	**×**	**×**

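### The carry-forward rule for withdrawn participants covers safety, so an early leaver who is not retested could be counted as having no laboratory change, and a second rule may say otherwise

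*Protocol article*

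**What the plan says.** Section 2.8.1 sets the rule for withdrawn participants: "The last available observation will be used as the final outcome for both efficacy and safety analyses". It is the only missing-data rule in the article that names safety.

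Table 2 in section 2.15 lists the safety assessments, introduced by "We will assess the safety of acupoint embedding therapy through the collection of biological sample information". Complete blood count, liver function, kidney function and ECG are marked at weeks 0 and 8 and at no other visit.

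Section 2.21 plans the safety analysis as "summarizing the incidence of adverse events and changes in laboratory parameters by treatment group using descriptive statistics", in the safety population. The same section contains two other missing-data statements. One is general: "preference will be given to filling in missing values using existing data through multiple imputation or mixed-effects models". The other comes at the end, after sentences about adverse events, subgroup analyses and multiplicity: "The analysis will handle missing data using a complete-case approach without imputation".

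Section 2.18 says that for dropouts "an early termination visit was organized to obtain primary/secondary efficacy outcomes (with consent), safety data, reasons for withdrawal, and final medication records". It does not say which laboratory tests are repeated.

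**The concern.** Carrying the last value forward needs a value recorded after treatment started. For the Table 2 tests there is no scheduled draw between baseline and week 8, so for someone who leaves in that window and is not retested, the last available value is the pre-treatment one. Final value minus baseline is then zero by construction, although nothing was measured after the first session.

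Two things are at stake. The mean laboratory change in an arm would shrink towards zero, and a table built this way would not show how many participants had no post-treatment test. Section 2.8 withdraws participants for missed visits, serious adverse reactions and changes in medical condition. The first group may well miss a retest; in the other two, laboratory safety matters most. The laboratory summary is one of the two safety summaries that section 2.21 describes.

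**Working it through.** **The plan's own figures (section 2.11).** With the stated formula:

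- (1.96 + 0.84)² × [0.60 × 0.40 + 0.25 × 0.75] / (0.60 − 0.25)² = 7.84 × 0.4275 / 0.1225 = 27.36, rounded up to 28 per arm.
- 28 / (1 − 0.20) = 35 per arm, which agrees with "After adjusting for a 20% dropout rate, the final sample size was determined to be 35 participants per group".
- Planned dropouts per arm: 0.20 × 35 = 7.

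**What each rule does with one participant.** Take someone who leaves before week 8 and has a week 0 value only.

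| Rule | Treatment of the missing Table 2 value |
|---|---|
| 2.8.1, carry-forward (names safety) | Final value = week 0 value, so change = 0 |
| 2.21, complete case (scope unclear) | Participant omitted, if the rule reaches safety |
| 2.21, multiple imputation or mixed model (general) | Value modelled, if the rule reaches safety |

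The three treatments differ, and the article does not say which one governs the laboratory summary.

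**Size if carry-forward is applied.** Let n = 35, let k be the number of untested leavers before week 8 in an arm, and let d be the mean change among those tested. Then:

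- Reported mean = [(35 − k) × d + k × 0] / 35 = d × (35 − k)/35.
- Relative dilution = k/35.

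| k | Dilution |
|---|---|
| 1 | 1/35 = 2.9% |
| 2 | 2/35 = 5.7% |
| 3 | 3/35 = 8.6% |
| 4 | 4/35 = 11.4% |
| 7 (all planned dropouts, all early, none retested) | 7/35 = 20% |

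The article gives neither the timing of dropout nor the retest rate, so k is an assumption. As an illustration only, suppose the 7 dropouts are spread evenly over the period in "Participants will be followed through week 32 to evaluate long-term therapeutic durability". Then 7 × 8/32 = 1.75 leave before week 8. The dilution is 1.75/35 = 5.0% if none is retested and 0.875/35 = 2.5% if half are.

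**What is not touched.** The Table 1 blood tests (ESR, CRP, lipids, glucose, uric acid) are also drawn at week 4, so the argument is not made for them. The adverse event rate in section 2.21 is a count of affected participants over those treated and uses no final value.

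**The case against.** The strongest reply is that the article does not commit itself to reporting zero change. The complete-case sentence stands a few lines below the description of the laboratory summary. If it applies there, untested leavers are simply left out, which is the right result. Nor does 2.8.1 say in terms that a week 0 value counts as an outcome observation. This stands in part: a reader might infer that zeros will certainly be entered, and the documents do not support that. They do support a literal rule that produces zeros and a neighbouring rule of unclear scope that does not.

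Second, the early termination visit collects safety data. If the blood tests are repeated there, the last available value is a post-treatment one and the carry-forward problem for those participants largely goes away. An article may fairly leave the exact panel to the full protocol. This also stands, and it narrows the point to leavers before week 8 who are not retested.

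Third, the size rests on assumed timing and retesting, and 35 is the randomised arm, whereas the summary uses the safety population. That is correct. The figures are a range, and 20% is a bound rather than an expectation.

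A reader might also infer that the rule makes the active arm look safer. Nothing in the article shows that untested early leavers would be more common in one arm, so no direction of bias between arms can be claimed.

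**Conclusion.** The point holds as a minor one. The only rule that names safety for withdrawn participants allows a pre-treatment value to stand as the final result. Combined with the week 0 and week 8 schedule, it could record untested people as unchanged, and it conflicts with the complete-case sentence if that sentence covers safety.

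The possible dilution of a mean laboratory change is k/35 per arm, with k unknown and bounded at 20% under the planned dropout. This assumes that all 35 are in the safety population and that everyone else has a post-baseline test. The same could happen to ECG data if they are summarised as change. The summaries are descriptive, so no test, primary conclusion or adverse event rate depends on the rule.

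**What to change.** In section 2.8.1, reword the sentence so that carry-forward no longer covers safety. Deleting both the word *both* and the words *and safety* leaves a grammatical sentence.

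In section 2.21, add that safety laboratory and ECG data are summarised from observed post-baseline values only, including early-termination and unscheduled results, with no carry-forward and no imputation. Add that the number with a post-baseline test is given by arm.

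The cost is a few words and one count per arm in the safety table, with no new visits, tests or participants. The downside is fewer values in the laboratory-change table. The change cannot recover an abnormality that nobody tested for, but it makes the number of untested participants visible. It also leaves open a separate question, the conflict between carry-forward in 2.8.1 and the mixed model planned for efficacy in 2.21, which needs its own correction.
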